##### High-intensity remote physical exercise program guided daily by HRV

Although all participants will daily measure their HRV, only in this intervention group each day's results will influence their exercise intensity. From the outcomes reported with smartphone photoplethysmography, explained the measurement process in the outcomes part, the root means squared differences of successive RR intervals (rMSSD) will be chosen as a reflection of vagal activity to prescribe the workout intensity [50]. In this regard, the natural logarithm of rMSSD will be calculated to make parametric statistical comparisons assuming a normal distribution. For establishing the training intensity and load, a 7-day rolling average measure (LrRMSSD7day-roll-avg) will be utilized. Subsequently, the scoring obtained will be contrasted in the smallest worthwhile change (SWC) to analyze if the daily result is inside SWC upper and lower limits, calculated as LnrMSSD reference week mean ± 0.5 × SD [51, 52]. The reference week of the first 4 training weeks will take the limits created in the baseline week, and in the rest of the program, an updated measure will be carried out every 4 weeks with the SWC for the past 4 weeks, because of the influence of exercise in participants cardiac autonomic modulation [53].

In this regard, when the daily LnrMSSD fell inside the limits created by the SWC patients will perform high-intensity training characterized by a cardiovascular intensity from 80 to 95% of their reserve HR (increasing a 5% every four weeks) and a weighting load from 70 to 85% of their RM (increasing the load 5% ever mesocycle, four weeks). Whereas if any day patients’ scoring fell out of the SWC, they will train at the same intensity as the PEG (Fig. 2).

**Fig. 2 Fig2:**
[figure not shown]
Intensity progression and intensity decision making process for the high-intensity exercise guide by HRV group

#### Usual care control group

Participants who will be allocated to the CG will participate in the before and after intervention assessments will measure daily their HRV. They will be advised to continue with their regular activities of daily living without any exercise restrictions.

### Outcomes

The following outcomes will be assessed in person by the oncology group at the hospital (Marqués de Valdecilla Hospital) or by a physical exercise professional at the sports center (GOfit) when it corresponds. The evaluations will be carried out before, after the intervention and 3 and 6 months after the end of the intervention to all the participants (HRVG, PEG and CG). To ensure CG measurements and follow up evaluations the principal investigator will call or write participants each month.

#### Physiological outcomes

##### Cardiotoxicity measurements

Cardiotoxicity will be assessed at the hospital to have a more exhaustive control and safety of the participants and at the end of the program. On the one hand, ç hemograms will be carried out to assess of High-Sensitivity Cardiac Troponin, Troponin I, N-terminal portion of B-type natriuretic pro-peptide (NT-proBNP), Troponin T due to their predictive values of cardiac damage in patients under the effects of chemotherapy [54, 55]. Although these variables were primarily planned in the trial registration, the hospital will be only able to assess High-Sensitive Cardiac Troponin and NT-proBNP.

In addition, an echocardiogram will be performed to measure the left ventricular ejection fraction and GLS due to its modification caused by cardiotoxicity [56–58] together with mean and maximum aortic valve gradient, ventricles’ diameters and thicknesses and valve velocities because their possible aortic stenosis risk [59]. Moreover, a resting electrocardiogram will also be performed on each patient to obtain values for heart rate, heart rhythm, heart rate variability, I-axis and aVF, Q-T interval, QRS complex, S-T segment and T-wave [60].

##### Measurement of biomarkers

On the one hand, the measurement of the following biomarkers will be included: Tumor Necrosis Factor, interleukins IL-6, IL-8 and IL-1b, C-reactive protein, creatine kinase, global lactate dehydrogenase, alkaline phosphatase, bilirubin levels, monocyte chemotactic protein and vitamin D. On the other hand, the anti-inflammatory cytokines IL-1ra and IL-10 [61]. As occurred in the cardiotoxicity variables, the interleukins will not be able to be measured at the hospital.

##### Lipid profile and glucose measurement

Apart from the mentioned outcomes, other variables from the patients' blood tests related to cancer prognosis and cardiovascular risk will be taken. Triglycerides, low-density lipoproteins and high-density lipoproteins will be collected due to their association with cancer prognosis and mortality [62]. Relatedly, fasting glucose will be analyzed because of its relation to metabolic syndrome in breast cancer survivors [63]. Other serum and hematological analyses will be done to control exhaustively each of the patients.

##### Blood pressure and resting heart rate measurement

Blood pressure measurements will be taken using a validated oscillometer Omron Healthcare Oscillometer [64]. The participants will remain at rest for five minutes before the assessment and will be lying in a supine position with the legs and arms completed. They will place their left or right arm, depending on the affected breast, straight, so that the cuff is at the level of the heart, 2 cm from the elbow. In addition, any clothing that may alter the results will be removed. Once in this position, the air tube of the cuff will be placed on the front of the arm aligned with the middle finger and with the blue date on the cuff. Systolic and diastolic blood pressure data will be taken; and, subsequently, the mean arterial pressure will be calculated by the following formula [(systolic blood pressure + (2 × diastolic blood pressure))/3] [65].

The resting heart rate will be measured for 5 min. The participants will lie relaxed in the supine position on a stretcher isolated from the floor. This data will be essential for the correct prescription of the intensity.

##### Heart rate variability and heart rate in rest measurements

The assessment of heart rate in rest and HRV will be performed by the Polar H10 chest strap and by photoplethysmography (PPG) with the validated mobile app of HRV4training [50, 66]. The participants will remain in the supine position for 8 min to obtain 5 min of a stable signal. After removal of artifacts, by employing the Kubios® clinical software the temporal variables of standard deviation time domains of all RR intervals (SDNN), rMSSD, Average of all NN intervals (AVNN) and percentage of differences between adjacent NN intervals that are greater than 50 ms (pNN50) will be calculated [67]. Moreover, by also utilizing Kubios software the frequency measurements of low frequency (LF, 0.04–0.15 Hz), high frequency (HF, 0.15–0.4 Hz) and the LF/HF ratio will be obtained [67]. The HRV4Training app directly calculates the HRV outcomes.

On the other hand, daily heart rate variability (HRV) is measured using the HRV4Training application, a validated mobile application [50, 66] that allows HRV values to be obtained by PPG (rMSSD, LF, HF, SDNN, SDNN, AVNN, pNN50 heart rate and recovery points). The morning measurement will be performed every day, in the supine decubitus position upon awakening, for 1 min. During the basal week before starting the intervention, participants will measure their HRV, to establish the reference values for each participant of the GHRV group. In the intervention weeks, the participants will measure their HRV every morning, therefore, collecting morning HRV data (rMSSD, heart rate and recovery points). The value that will be taken into consideration to establish the GHRV training intensity will be the rMSSD as it represents the parasympathetic activation of the central nervous system. The detailed information of its utilization to exercise prescription is explained in the exercise program intervention part. To eliminate the placebo effect of the use of the application, the participants of the three physical exercise groups will perform this protocol. In this way, the HRV data of all the participants will be collected to analyze their evolution with the different interventions. To reduce measurement error, the application functioning is explained to all participants, mentioned to repeat the measurement if a message saying that the sign was not optimal or poor the need to repeat it. Moreover, the exercise professional will check the quality of the sign before its analysis.

##### Body composition measurement

The assessment of the percentage of fat and the visceral level of the participants are variables to be taken into consideration, due to the existing risk in women with overweight and obesity, of a greater relapse in breast cancer [68] and the possible effective role of high-intensity exercise [69]. Therefore, by utilizing the impedance Inbody analyzer [70] the body fat mass [68], body fat percentage, visceral fat level, musculoskeletal mass, body water, the bone mineral content, segmental fat mass (trunk, right and left arm and right and left leg) and segmental lean mass (trunk, right and left arm and right and left leg) of the patients will be evaluated [71]. In addition, all participants will be weighed and measured to obtain their Body Mass Index (BMI) by the formula of [weight/height^2^].

##### Measurement of anthropometric parameters

Patients will use a non-elastic tape measure for the evaluation of waist circumference, hip circumference, chest circumference, arm circumference, leg circumference following the guidelines set by the American College of Sports Medicine [72].

#### Physical exercise evaluations

##### Cardiorespiratory fitness measurement

To record the cardiorespiratory capacity, maximum heart rate and the patients' perception of effort, the Bruce incremental submaximal test (modified) [73] will be performed on a treadmill. During the test, the patients will wear a Polar H10 chest strap to monitor their heart rate. Thus, following the protocol created by Bruce, the treadmill will start with a 0% incline and a speed of 1.7 m/h which will be maintained during the first 3 min. Every 3 min both the speed and the incline will be increased until the participants decide that their fatigue is too high to continue. In addition to constant heart rate monitoring to record the maximum heart rate, the patient will be asked about her perception of exertion every minute. By acquiring the maximum heart rate we can then prescribe the target intensity from the reserve heart rate using Karvonen's formula [74]. At the end of the test, the recovery heart rate will be recorded 1 min after stopping the test in order to assess the recovery rate. Subsequently, the maximum oxygen consumption of each patient (VO_2max_ = 2.282* (time) + 8.545) will be calculated from the formula proposed by the creators. This submaximal test has been commonly used in cancer patients in different exercise interventions [75].

##### Lower and upper body strength measurement

Lower body strength resistance. For the measurement of the lower body strength resistance, the 30 s chair stand test will be used. The patients will use a chair without armrests, with the back against the wall so that it does not move during the test [76]. The evaluation will begin with the participant seated in the middle of the chair with arms flexed at the chest and hands resting on the opposite shoulder of the chair. The patient will stand up, positioning herself fully stretched, and will sit the maximum number of repetitions possible in 30 s. During the development, the patient will be encouraged and reminded of the need to sit down completely for each repetition. The number of repetitions achieved is recorded. This test has been performed previously in breast cancer survivors [37].

Upper body strength resistance. As for upper body strength- endurance, the patients will be measured by the 30-s arm curl test of the Senior fitness Manual [76]: a 2.5 kg weight will be used according to the Senior fitness Manual. The participants will be seated in a chair and with the dominant arm, they will have to perform elbow flexion extensions starting in full extension. The test will report the maximum number of repetitions in 30 s [76]. This assessment has been used previously in the breast cancer population [77, 78].

Lower and upper maximum force, velocity, and power. The evaluation of the maximum force will be carried out by using a linear encoder for the correct calculation of the maximum weight that the patient can lift in one repetition (RM) from the speed and power generated when moving the weight vertically. For the easy and correct performance, the different tests will be carried out on a multipower machine with a counterweight mechanism which will guide the vertical movement in a rectilinear way without the influence of the barbell weight.

The participants will begin to perform each of the exercises using the barbell as the only weight for 3 repetitions as a warm-up. After, at least three incremental weight discs will be added depending on the exercise and the patient's perception of effort and the speed of execution decline. At the end of each repetition, patients will be asked about their perception of perceived exertion using the modified Borg scale (Rate of Perceived Exertion, RPE) [79] and when this value has dropped to 2/10, the next weight will be added.

Diverse variables will be analyzed in each of the repetitions by employing the Chronojump by Boscosystem linear encoder, the MyLift mobile app [80] or the kinovea software [81] See supplementary table. So that, each participant’s repetition will be recorded by an iPhone camera of 240 frames per second.

This protocol will be repeated for each of the following exercises:Barbell Squat (Back Squat Test). Participants will hold the bar behind the back of their neck with the weight resting on their shoulders. If they have difficulty maintaining this position, the evaluation will be done by holding the bar in front of them under their neck with their arms crossed. Start with your knees fully extended and your feet shoulder-width apart. You will progressively bend your knees, without exceeding the line of the toes, until you reach 90° of flexion. Once you have reached this point, you will recover the initial position by extending your knees.Deadlift Test. Participants will begin the movement with feet hip-width apart, hands in the centre of the bar (placed on the floor) and shoulder-width apart, the bar will be placed close to the shins and the knees bent until the hands can grasp the bar. The chest should remain upright and the back straight throughout the exercise. The hips should be above the knee so that the shoulders are positioned in front of the bar. The movement starts with a slight knee extension, followed by a hip extension and ends with a simultaneous knee and hip extension until the shoulders are positioned behind the bar, thus aligning the whole body [82].Lunge Test. Participants will start the movement by placing their feet shoulder-width apart, holding the bar behind the back of their neck, leaving the weight of the bar on their shoulders. They will take one step forward. The distance of this will correspond to the distance from the superior iliac spine to the medial malleolus of the tibia. Once this distance is reached, bend the knees, touching the floor with the back knee and reaching 90° of flexion in the front knee. Subsequently, they will recover the initial position by fully extending the front leg and progressively transferring the weight of the body to the back leg [83].Chest press (Chess press). Participants lie on the bench with their legs bent to the sides of the bench at slightly more than 90°. They will grasp the bar with their hands wider than shoulder-width apart. The movement will begin with the elbows fully extended and with the bar at throat level. Progressively lower the bar by bending the shoulders, followed by bending the elbows until the bar reaches one centimeter from the chest. Once the maximum flexion is achieved, they will extend the elbows and shoulders until they return to the initial position [37, 84].Shoulder press. Participants sit on the bench with their backs against the backrest. Start the movement by grasping the bar with elbows fully extended with hands 5 cm wider than shoulder-width apart. Lower the bar continuously until it comes into contact with the upper chest. Then start the concentric phase by extending the elbows completely to the starting position [85].Bent over row. Participants perform the exercise with their backs bent at 45°. They begin the movement by holding the bar in front of their shoulders with their hands shoulder-width apart. Proceed to bend the elbows, bringing them behind the body until the barbell touches the middle of the abdomen [86].Biceps curl with barbell. Participants will stand in an anatomical position with knees slightly bent and feet apart. They will hold the bar with a supine grip, arms parallel to the sides of the body. Begin the movement with elbows fully extended and progressively bend the elbows to their maximum. Subsequently, they will extend their elbows to the starting position [87].

Finally, the strength-power will be measured by employing a countermovement jump test (CMJ) and from squat (SJ) to evaluate the explosiveness of the patient, as has been done in previous studies on patients with breast cancer [88]. it was decided to eliminate the assessment of hip trust and triceps barbell strength, included in the clinical registration because performing all the tests would take too long for the patients.

Vertical applied force. The force-power will be measured utilizing a CMJ and from SJ as a reflection of the application of force in the unit of time, inter and intramuscular coordination and the use of the elastic energy of those actions in which the stretch–shortening cycle of the lower limbs predominates, which is present in the majority of actions in daily life, as has been carried out in previous studies in patients with breast cancer [88]. In the evaluations after the intervention, those patients in whom it is possible to evaluate the jump with progressive loads, the vertical force–velocity profile will be performed, which will give us information on how the subject is currently producing power and how it should (based on their characteristics) in order to be able to evaluate the explosiveness of the patients [89]. To obtain it, together with the SJ and CMJ jumps without load, the patients will perform 2–3 more attempts with progressive loads, determining the increase in load according to the height of the jump without weight [90]. In addition, for the corresponding calculations, two body measurements will be taken to determine the push-off distance (pod). For the evaluation of the different variables indicated, different technologies will be used such as the Chronojump’s contact platform and the recording with an IOS camera of 240 f.p.s of each of the jumps for subsequent analysis with the validated application of My Jump [91] and Kinovea [92].

 Horizontal applied force. For the evaluation of this manifestation, of force, an acceleration action will be recorded (the only requirement is to start from speed 0 and to cover a distance of 30 m in the shortest possible time, the time used not being a limitation for the performance of the test). This recording will be used to calculate the horizontal force–velocity, which will give a mechanical description of how the patient has applied forces to move horizontally. For the complete assessment of the horizontal profile in the post-intervention evaluation, patients will perform 3 progressive 30 m sprints by running or walking (at 50%, 70% and 90% of the participants' maximum self-perceived speed) [93]. For this, an IOS device with 240 frames per second will be used and subsequently analysed with the validated App for IOS devices (My Sprint) [94]. The device, iPhone will be mounted to a tripod (in the frontal plane) to film the sprint from the side, at the 15 m marker and at 18 m from the track, to register the entire sprint. Since the iPhone 6 was in a fixed position, video parallax was corrected to ensure 5 m, 10 m-, 15 m-, 20 m-, 25 m and 30 m split times were measured properly.

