### Statistical analysis

All the outcome results will be included in an anonymous database to conduct the statistical analyses. A descriptive, quantitative, and graphics analysis will be performed of all the included variables. The statistic software employed will be the IBM Statistical Package for the Social Sciences (version 25.0; SPSS, Inc., Chicago, IL, USA) [115]. The number of statistical analyses will be high and diverse depending on the nature of the results. In general, we will proceed with the usual steps to check the normality and homogeneity of variables.

First, the Kolmogorov–Smirnov and Shapiro Wilk tests will be used to determine whether parametric or non-parametric statistical analyses should be applied to each of the variables analyzed. In this regard, normal distribution will be assumed when the p-value is greater than 0.05 indicating that the variable tested was not significantly different from a normal distribution. Descriptive results will be presented as mean and SD or median (range) according to the results of the normality tests. Subsequently, to evaluate the effects of the program, a repeated-measures ANOVA or Kruskal–Wallis, depending on the normal distribution, will be used. The interaction factors of the ANOVA, or Kruskal–Wallis, will be the group (HRVG, PEG or CG) and the timing of the measure (before, after the intervention and follow-up). Besides, a Bonferroni analysis will be performed to adjust the results. Results shall include the Cohen’s d effect size (95% confidence interval) and statistical significance for each dependent variable concerning time and its interaction effects (group × time). Moreover, to analyze the differences between the group independently in each of the variables, the T-test for Independent Samples and the T-test for related samples, or a Mann–Whitney U-test or Wilcoxon in case of not fulfilling the principle of normality, will be employed.

Concurrently, a correlation analysis is planned to be done to establish novel relations between some of the measures performed. For instance, a Pearson o Spearman analysis (depending on the results of the normal distribution analysis) will be calculated between the change in strength, the body composition, cardiotoxicity variables and the psychological variables. Moreover, a correlation between the results obtained in the different questionnaires will be calculated.

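### The vertical force–velocity profile is taken only after the intervention and only in patients able to do loaded jumps, yet the analysis section tests every variable between arms and over time without exempting it.

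*Protocol article*

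**What the plan says.** Under Lower and upper body strength measurement, the paragraph on vertical applied force describes unloaded squat jumps (SJ) and countermovement jumps (CMJ), with no restriction on who does them. It then adds a force–velocity profile with two limits, one on timing and one on patients: it is done at the evaluations that follow the intervention, and in "those patients in whom it is possible to evaluate the jump with progressive loads". To obtain it, "the patients will perform 2–3 more attempts with progressive loads, determining the increase in load according to the height of the jump without weight". The article gives no criterion for when the loaded test counts as possible, and no rule for patients who cannot do it.

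This departs from the general schedule under Outcomes: "The evaluations will be carried out before, after the intervention and 3 and 6 months after the end of the intervention", for all participants in all three groups.

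The Statistical analysis section makes no exception for the profile. It plans, "to analyze the differences between the group independently in each of the variables, the T-test for Independent Samples" or the Mann–Whitney test. It also promises an effect size and significance for time and for group × time on each dependent variable, with a time factor that includes the measurement before the intervention.

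**The concern.** A between-arm test is protected by randomisation when everyone randomised can contribute. Here a patient contributes only if she can jump with added load, and that is judged after the arms have been treated differently. Both exercise groups train squats, lunges, deadlifts and hip thrusts (Physical exercise programs, Table 1). The control group continues its usual activities (Usual care control group).

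If training makes some weaker patients able to do the test, the exercise arms will be profiled further down the strength range than the control arm. A higher-is-better result would then be pulled against exercise, and a real benefit could look smaller or absent. With no profile before the intervention, imbalance in the profiled subset cannot be adjusted for on this measure, and change from baseline cannot be tested.

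**Working it through.** The article states no figure for the profile, so there is none to reproduce. The check asks how large the distortion could be if the analysis section were followed literally.

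**From the article**
- Profile after the intervention only, in able patients only (vertical applied force paragraph).
- Between-group and group × time tests on every variable (Statistical analysis).
- 90 patients in three groups, 20% dropout (Sample size). With equal allocation, which is an assumption, 90 / 3 = 30 per arm, and 30 × 0.8 = 24 remain.

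**Assumed, because the article does not give them**
- Ability is normal with SD 1, and a patient is profiled if it exceeds a fixed threshold c.
- Training raises ability by d = 0.3 to 0.8 SD, equally for every patient.
- 30% to 90% of controls are able.
- The profile outcome has SD 1, higher is better, and it correlates ρ = 0.5 to 0.8 with the pre-training part of ability.

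**Formula.** Let λ(t) = φ(t) / (1 − Φ(t)), the mean of a standard normal variable above t. Among profiled patients the mean outcome is ρ·λ(c) in control and δ + ρ·λ(c − d) in an exercise arm, where δ is the true effect. So

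observed difference = δ + ρ·[λ(c − d) − λ(c)],

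and the second term is the bias.

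**Central case: half of controls able (c = 0), d = δ = 0.5**
- Able: 50% of controls, and 1 − Φ(−0.5) = 69% of an exercise arm. Of 24, that is about 12 versus 17.
- λ(0) = 0.3989 / 0.5 = 0.798. λ(−0.5) = 0.3521 / 0.6915 = 0.509. Difference: −0.289.

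| ρ | Bias (SD) | True 0.5 SD is seen as |
|---|---|---|
| 0.5 | 0.5 × (−0.289) = −0.144 | 0.36 |
| 0.8 | 0.8 × (−0.289) = −0.231 | 0.27 |
| 1 (extreme) | −0.289 | 0.21 |

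With no true effect on the outcome (δ = 0), the exercise arm would look worse by 0.14 to 0.23 SD for ρ of 0.5 to 0.8.

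**Range**

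| Controls able | λ(c) | d | λ(c − d) | Bias, ρ = 0.5 | Bias, ρ = 0.8 |
|---|---|---|---|---|---|
| 30% (c = 0.524) | 1.159 | 0.3 | 0.946 | −0.11 | −0.17 |
| 30% | 1.159 | 0.8 | 0.631 | −0.26 | −0.42 |
| 90% (c = −1.282) | 0.195 | 0.3 | 0.121 | −0.04 | −0.06 |
| 90% | 0.195 | 0.8 | 0.047 | −0.07 | −0.12 |

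With d = 0, λ(c − d) = λ(c) and the bias is zero. A simulation of the same model with 2,000,000 patients per arm agrees to within 0.01 SD (for example 0.35 in place of 0.36 in the central case).

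**The case against.** The best defence is that the article never names the profile as a between-arm endpoint. Its stated use is largely individual: "which will give us information on how the subject is currently producing power and how it should". It is not listed in the aim, and the sample size rests on VO2peak and global longitudinal strain. This stands as a limit on importance. It does not remove the problem, because the analysis section covers each variable and exempts none.

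Differential selection is also assumed, not shown. Inability might reflect pain, injury or technique and be equal across arms. The aim's leading comparison is between the two exercise groups, which follow the same circuits with different loads and repetitions, so ability probably differs less there. This stands too, and it is why the point concerns chiefly exercise versus control.

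Four stronger readings are tempting, and the document does not support them:

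- A reader might infer that more than half of a real effect is lost (0.21 seen of 0.5 SD). That requires the outcome to be the very ability that selects patients. At correlations of 0.5 to 0.8 the loss in the central case is 0.144 / 0.5 = 29% to 0.231 / 0.5 = 46%, and it is smaller if nearly all patients are able.
- A reader might infer that the bias always runs against exercise. That holds for higher-is-better quantities. The article also describes judging the profile against how the individual should produce power, so the direction is not settled for every derived quantity.
- A reader might infer that no group × time test is possible. The text refers to evaluations after the intervention in the plural, and visits at 3 and 6 months are scheduled, so a test across those visits may be feasible. What is lost is change from baseline.
- A reader might extend the selection argument to the horizontal profile. Its complete form is also done after the intervention, but patients may run or walk and there is no ability restriction.

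**Conclusion.** The point holds as a minor one. Followed literally, the article tests arms on a subset whose membership training may change, on a measure with no value before the intervention. That comparison is not protected by randomisation.

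The size cannot be known from the article. Under the normal-threshold model, a higher-is-better quantity is biased by about −0.04 to −0.42 SD over the ranges assumed. The bias is at most about 0.12 SD if 90% of controls can do the test, and nil if ability does not differ by arm. No main conclusion of the trial depends on this measure.

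**What to change.** Add a sentence to Statistical analysis that exempts the vertical force–velocity profile from the between-arm and group × time tests. Report it descriptively, with the number and proportion of patients able per arm and the reasons for inability. Base the arm comparison of explosive strength on unloaded SJ and CMJ, which are described without the ability restriction.

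Ranking patients unable to do the test as worst would keep a test, but the article names no ordered quantity from the profile, and the ranking would score patients who could not be tested for other reasons as poor performers. The descriptive route is safer.

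The cost is one or two sentences, recording why a patient was not profiled, and giving up an inferential arm comparison on this one secondary measure.
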